## Abstract

**Background:**

Pain and anxiety caused by vaccination and other medical procedures in childhood can result in discomfort for both patients and their parents. Virtual reality (VR) is a technology that is capable of entertaining and distracting the user. Among its many applications, we find the improvement of pain management and the reduction of anxiety in patients undergoing medical interventions.

**Objective:**

We aim to publish the protocol of a clinical trial for the reduction of pain and anxiety after the administration of 2 vaccines in children aged 3 to 6 years.

**Methods:**

We will conduct a randomized, parallel, controlled clinical trial with 2 assigned groups. The intervention group will wear VR goggles during the administration of 2 vaccines, while the control group will receive standard care from a primary care center for the procedure. Randomization will be carried out by using the RandomizedR computer system—a randomization tool of the R Studio program. This trial will be an open or unblinded trial; both the subjects and the investigators will know the assigned treatment groups. Due to the nature of the VR intervention, it will be impossible to blind the patients, caregivers, or observers. However, a blind third-party assessment will be carried out. The study population will include children aged 3 to 6 years who are included in the patient registry and cared for in a primary care center of the region of Central Catalonia. They will receive the following vaccines during the Well-Child checkup: the triple viral+varicella vaccine at 3 years of age and the hepatitis A+diphtheria-tetanus-pertussis vaccine at 6 years of age.

**Results:**

The study is scheduled to begin in January 2022 and is scheduled to end in January 2023, which is when the statistical analysis will begin. As of March 2022, a total of 23 children have been recruited, of which 13 have used VR during the vaccination process. In addition, all of the guardians have found that VR helps to reduce pain during vaccination.

**Conclusions:**

VR can be a useful tool in pediatric procedures that generate pain and anxiety.

**International Registered Report Identifier (IRRID):**

PRR1-10.2196/35910

## Introduction

Pain is defined as a complex and multidimensional sensory experience that comprises cognitive, behavioral, and psychological elements [1,2]; it is usually associated with unpleasant and subjective experiences and involves an adaptive function that allows for the initiation of protective responses [2]. Fear and stress influence the perception of pain, and the failure to apply appropriate pain reduction techniques exposes patients to unnecessary negative experiences, which can lead to long-term consequences, such as needle phobia or anxiety about medical procedures [2-4].

Pediatric patients seen in primary care settings frequently experience negative reactions, such as fear, anxiety, pain, or feelings of aggression, during routine invasive procedures, such as vaccinations, blood draws, wound sutures, or nursing care.

According to the World Health Organization, the possible adverse reactions to vaccination that are linked to procedural stress include fainting, hyperventilation, vomiting, and seizures [5]. Further, 19% of patients aged 4 to 6 years have needle phobia [6], with the average age of onset being 5.5 years [7]. Additionally, 7% of children experience syncope (fainting) during the administration of a medical injection, and 5% avoid treatment [8]. In a study on the impact of the fear of needles on adherence to vaccination, it was estimated that fear was the cause of nonadherence in 8% of children [9].

For all of these reasons, different mechanisms have been developed to try to minimize or eliminate adverse reactions to vaccination [2]. In the clinical practice guidelines for reducing pain during the administration of vaccines in the pediatric age group [10,11], the following main recommendations are made: breastfeeding during the procedure, offering sweet solutions before vaccine administration to those older than 1 year if they cannot be breastfed, and comfortably positioning patients if they can be held by their parents or using a rapid vaccination technique without aspiration.

Distractions help to reduce anxiety because they prevent painful stimuli from being transmitted either to the thalamus (ie, to the limbic system) or to the sensory cortex in such an effective way [12,13], thereby helping one to focus their attention on external and internal stimuli and not on nociceptive stimuli [14,15]. Distractions sometimes surpass local anesthetics’ ability to control pain and discomfort associated with medical interventions [12]. Distractions can be active (immersive), which involves patient participation through the manipulation of the environment, or passive (nonimmersive), which involves observation only [13].

Current technological advances, especially in the field of virtual reality (VR), have resulted in new types of distractions, which can be used along with traditional distractions [14] to achieve better pain control in pediatric patients for procedures such as vaccination, according to the *Protocol of Preventive and Health Promotion Activities in Pediatric Patients: Healthy Childhood* [15].

*VR* is a term that was proposed in the mid-1980s by Jaron Launier, and it refers to a computer technique that allows for the creation of a simulated environment by means of a device with sensors that can be connected to a computer, mobile device, or tablet [1,3]. Its effectiveness is based on the psychological theory of “presence” [2,3]. This theory posits that people interact with their environments via the following three types of components: auditory, visual, and tactile components [1,2]. VR technology redirects one’s attention to a more pleasant environment [2] by replacing real stimuli with virtual stimuli. This activates users’ higher cognitive and emotional brain regions, resulting in the dissociation of pain [2,3].

The idea behind VR-generated analgesia was probably inspired by the intercortical modulation of pain matrix signaling pathways via attention, emotion, memory, and other senses [12,13].

In a systematic review published by the Cochrane Library in 2019 on VR distraction for reducing acute pain in children, it was concluded that the use of VR had low evidence regarding its benefits. However, in that review, due to the limited amount of data available, no conclusions could be drawn about the side effects of VR, satisfaction with VR, the level of parental anxiety, or the cost of VR use [12].

Many aspects remain to be clarified; however, the use of VR for pain management has shown great benefit in hospital procedures. Our study seeks to introduce VR as an analgesic tool in pediatric primary care services and daily procedures, such as vaccination, thereby combining new technologies with traditional concepts, such as distraction [1-3].

## Methods

### Study Design

#### Trial Design

We will conduct a randomized, single-center, open, parallel, and controlled clinical trial with 2 assigned groups (intervention group and control group).

#### Scope and Period of the Study

The study population will include children aged 3 to 6 years who are included in the patient registry and are being seen in a primary care center of the Catalan Institute of Health in Central Catalonia.

The study will be conducted during the period of January 2022 to January 2023. If the minimum sample size is not achieved, the study period will be extended until it is achieved.

#### Participants

##### Inclusion Criteria

The patients who will take part in the study will be those from the pediatric population (ie, those aged 3 to 6 years) in the register of patients from a primary care center of the Catalan Institute of Health in Central Catalonia who, according to the vaccination schedule, are due to receive 1 of the following 2 vaccinations: (1) the triple viral+varicella vaccine at 3 years of age and (2) the hepatitis A+diphtheria-tetanus-pertussis vaccine at age 6.

##### Exclusion Criteria

The exclusion criteria will include the following: (1) patients who have already received 1 of the 2 vaccines to be administered; (2) patients and accompanying persons who do not understand and speak Catalan or Spanish; (3) patients with physical or mental illnesses, as well as those with blindness or deafness; (4) patients with a known history of epileptic episodes or severe motion sickness; (5) patients with any infections, burns, or injuries to the face, head, or neck that may interfere with the placement of the VR device; and (6) the absence of legal guardians for signing the informed consent form.

#### Intervention

The intervention group will use the Pico G2 VR goggles (Pico Interactive Inc) during the administration of the two vaccines, together with an Android AOYODKG tablet, which will be connected to the goggles as a controller.

The control group participants will receive traditional distractors, such as being held by the parent or guardian who accompanies them to the appointment, receiving stickers at the end of the appointment, or receiving rewards that the parent or guardian has prepared from home.

Eligible patients will be invited to participate in the study on an ongoing basis, and the assignment to study groups will be randomized.

#### Randomization

##### Sequence Generation

Randomization will be carried out by using the RandomizedR computer system—a randomization tool of the R Studio program.

##### Implementation

The participants will be selected from a patient diary register. Both the sequence and the allocation of participants to the interventions will be generated by using the RandomizedR computer system.

##### Masking

Due to the nature of the study, it will not be possible to mask patients or health care professionals. Therefore, the trial will be open or unblinded. However, a blind evaluation by third parties will be carried out, as the person in charge of data analysis will not be involved with the intervention.

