### Data Collection and Sources of Information

#### Recruiting Patients to Participate in the Study

The procedure will be carried out by 1 pediatric team consisting of a pediatrician and a nurse of the primary care center in Súria (Spain). The families will be contacted by telephone to schedule the patients for the checkup at 3 and 6 years of age, as is currently done. The nurse will administer the vaccines and will continue to be part of the Well-Child checkup team.

Information on the purpose, risks, and benefits of the study will be provided, and any queries will be answered. In addition to verbal information, an information document about the study will be provided.

Prior to the start of the study, training on the use of the devices will be given to all of the health care personnel involved.

If a family agrees to be included in the study, the informed consent form must be signed by at least 1 of the parents or legal guardians. The signing parent or guardian will agree to inform the other parent or guardian.

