#### Data Collection, Sources of Information, and Intervention

Study data collection will begin once informed written consent has been obtained from the legal guardian. For patients’ assignment to a study group, randomization will be carried out by using the RandomizedR computer system. The person responsible for data collection will indicate the patients’ age, gender, and study group and the type of intervention performed. Prior to administering the vaccine, the patients’ condition and heart rate on arrival at the clinic will be recorded, regardless of their assigned study group.

For patients in the intervention group, it will be explained to them that they will be able to use the VR device; they will be assisted in fitting the device and will be given a brief explanation of the content that will be played. The *Leia's World* (VRPharma Immersive Technologies SL) content, which was specially designed for vaccination, will be used, and data will be collected before and after the procedure for each of the first 2 vaccinations.

The Wong-Baker Faces Pain Rating Scale, which ranges from 0 to 10, and the Children’s Fear Scale, which ranges from 0 to 4, will be used to evaluate the reduction of pain and anxiety. The data collected from the control group will be compared with those collected from the intervention group (heart rate, the level of pain perception, the level of distress and fear, and the length of visits) [17-19]. In addition, to understand the perceptions of the tutors on the use of VR, a satisfaction survey will be conducted [20].

The aforementioned data will be collected by the nursing or pediatric professional via a web questionnaire generated by the Microsoft Forms tool on the tablet and will be hosted in a computer server of the Institut Català de la Salut de la Catalunya Central.

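### The claimed blind third-party assessment rests only on an analyst who takes no part in the intervention; outcome reporting and recording, as described, are open-label

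*Protocol article*

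**What the plan says.** The Abstract (Methods) calls the trial open and says that "it will be impossible to blind the patients, caregivers, or observers". The next sentence reads "However, a blind third-party assessment will be carried out". The Abstract does not say who the third party is.

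The Masking section repeats that neither patients nor health care professionals can be masked, then says that "a blind evaluation by third parties will be carried out", and gives one reason: "as the person in charge of data analysis will not be involved with the intervention".

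The sections on recruitment and data collection describe who does the work:

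- Delivery: "The procedure will be carried out by 1 pediatric team consisting of a pediatrician and a nurse".
- Vaccination: "The nurse will administer the vaccines and will continue to be part of the Well-Child checkup team".
- Recording: "The aforementioned data will be collected by the nursing or pediatric professional via a web questionnaire".
- Content of the form: "The person responsible for data collection will indicate the patients’ age, gender, and study group and the type of intervention performed".

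The Statistical Analysis section names the sources of the pain and anxiety values: the children, their caregivers and the nurses.

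**The concern.** Blinded assessment has a definite meaning: whoever produces or judges the outcome does not know the arm. The article uses that language in two places, and the arrangement it then describes is something else. The main outcomes are a faces pain scale and a fear scale, used with children aged 3 to 6, together with guardian satisfaction. These are subjective, so a reader will look at masking first when judging how far to trust a difference between arms. Someone who reads only the Abstract, or who extracts the blinding status for a systematic review, could credit the trial with a safeguard that the described design does not contain.

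**Working it through.** No figure in the article bears on this point, so the check sets its statements side by side.

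**Step 1. Is there a masked outcome assessor?**

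| Role | Who, as described | Can they be masked, according to the article? |
|---|---|---|
| Reports pain and anxiety | Child | No (Abstract; Masking) |
| Reports pain and anxiety | Caregiver | No (Abstract) |
| Reports pain and anxiety | Nurse | No (Masking, as a health care professional) |
| Records the data, including heart rate and visit length | Nursing or pediatric professional | No (Masking; also the Abstract, if counted as an observer) |
| Analyses the data | Person not involved with the intervention | Not stated beyond the general word blind |

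Every role that produces or records an outcome falls in a group that the article says cannot be blinded. No independent or masked assessor appears elsewhere. The analyst is the only remaining candidate, and Masking confirms that the analyst is the person meant.

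**Step 2. Does analysis count as assessment?** The analyst receives scores that have already been elicited and entered. Masking at that stage protects choices made during the analysis, such as exclusions, handling of odd values or selection among models. It cannot act on how a score was given or written down. The reason offered therefore supports, at best, a statement about the analysis.

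**Step 3. Does non-involvement establish masking of the analyst?** A person can be absent from the clinic and still open a file that names the arm. The data collector enters study group and type of intervention on the web form, so the collected data identify the arm unless someone removes or recodes it. A guardian survey about the use of VR is collected as well, and answers to it could reveal the arm even if the group column were hidden. The article describes no recoding. The reason given is compatible with a masked analyst and with an unmasked one, so it does not establish either.

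**The case against.** The strongest reply is that nobody is misled. The article calls the trial open in the Abstract and under both Trial Design and Masking, and Masking identifies the third party as the analyst in the same sentence that makes the claim. That stands: this is an overstated label and not a hidden weakness. It does not fully rescue the Abstract, which makes the claim without the explanation.

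It can also be said that arm coding and code release are details for the full protocol or the analysis plan, neither of which is shown. That stands for the mechanism. It does not cover the claim itself, since no later document can turn an analyst into an outcome assessor.

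Four stronger readings are tempting and are not supported:

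- *The analyst is unmasked.* The article does not say so. Most trial databases hold the arm, and nothing shows that the analyst gets it uncoded. What can be said is that the reason given does not establish masking.
- *The person who scores the child is the one who gives the vaccine or fits the goggles.* With a single team of one pediatrician and one nurse this is likely, but it is an inference. The data collection section names only the profession.
- *The mislabelling inflates the false-positive rate by some amount.* The article gives no size for reporting or recording bias. Any assumed shift would apply equally to other open-label trials with such outcomes, and neither rewording nor coding the arms would remove it.
- *The child's own score must be declared primary.* That concerns the order of endpoints and is a separate matter from masking. A child who wears the goggles cannot be masked in any case.

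**Conclusion.** The point holds in a limited form. The article claims a blinded assessment in two places and supports it with a reason that establishes neither outcome assessment nor masking. On its own description, outcome reporting and recording are open-label and only the analysis is separate from delivery.

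The consequence is a misstated safeguard. The sample size, the planned tests and the estimates are unchanged, and no bias magnitude is attached. The conclusion rests on the published article alone and assumes that no masked assessor is described in an unseen full protocol. The Abstract's statement that observers cannot be blinded makes such an assessor unlikely. The correction is worth making because it concerns a main protection against bias in a trial with subjective outcomes, and it costs very little.

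**What to change.** 1. In the Abstract and under Masking, replace the blinded-assessment claim with a plain statement that outcome reporting and recording are open-label and that the analysis is done by a person independent of the intervention.
2. Choose one of two descriptions of the analyst and state it:
   - *Masked analyst.* Supply a dataset with the arms coded A and B, holding back the type of intervention and any fields that only VR participants would complete. Release the code after the primary analysis script is locked.
   - *Unmasked analyst.* Call the analyst independent and drop the word blind.

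The cost is the rewording, plus one recoded export if the first option is taken. It needs no extra staff and no change to sample size or clinical care. The drawback is that the stated level of blinding becomes less favourable. Neither option removes reporting or recording bias from the subjective outcomes, and the text should not suggest that it does.

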#### Sample Size Determination

To detect a 1-point difference between the two groups on the pain level scale, a sample of 150 boys and girls in each group is required, assuming an SD of 3 points, an α risk of 5%, a power of 80%, and an estimated loss to follow-up rate of 5% [16].

### Data Collection and Sources of Information

#### Recruiting Patients to Participate in the Study

The procedure will be carried out by 1 pediatric team consisting of a pediatrician and a nurse of the primary care center in Súria (Spain). The families will be contacted by telephone to schedule the patients for the checkup at 3 and 6 years of age, as is currently done. The nurse will administer the vaccines and will continue to be part of the Well-Child checkup team.

Information on the purpose, risks, and benefits of the study will be provided, and any queries will be answered. In addition to verbal information, an information document about the study will be provided.

Prior to the start of the study, training on the use of the devices will be given to all of the health care personnel involved.

If a family agrees to be included in the study, the informed consent form must be signed by at least 1 of the parents or legal guardians. The signing parent or guardian will agree to inform the other parent or guardian.

#### Data Collection, Sources of Information, and Intervention

Study data collection will begin once informed written consent has been obtained from the legal guardian. For patients’ assignment to a study group, randomization will be carried out by using the RandomizedR computer system. The person responsible for data collection will indicate the patients’ age, gender, and study group and the type of intervention performed. Prior to administering the vaccine, the patients’ condition and heart rate on arrival at the clinic will be recorded, regardless of their assigned study group.

For patients in the intervention group, it will be explained to them that they will be able to use the VR device; they will be assisted in fitting the device and will be given a brief explanation of the content that will be played. The *Leia's World* (VRPharma Immersive Technologies SL) content, which was specially designed for vaccination, will be used, and data will be collected before and after the procedure for each of the first 2 vaccinations.

The Wong-Baker Faces Pain Rating Scale, which ranges from 0 to 10, and the Children’s Fear Scale, which ranges from 0 to 4, will be used to evaluate the reduction of pain and anxiety. The data collected from the control group will be compared with those collected from the intervention group (heart rate, the level of pain perception, the level of distress and fear, and the length of visits) [17-19]. In addition, to understand the perceptions of the tutors on the use of VR, a satisfaction survey will be conducted [20].

The aforementioned data will be collected by the nursing or pediatric professional via a web questionnaire generated by the Microsoft Forms tool on the tablet and will be hosted in a computer server of the Institut Català de la Salut de la Catalunya Central.

### Statistical Analysis

An intention-to-treat analysis will be performed; the subjects will be analyzed according to the group to which they were initially assigned and not the group in which they finally participated.

The data will be obtained through Microsoft Forms (an application included in Office 365 [Microsoft Corporation] that allows one to create customized questionnaires, surveys, and records) and analyzed with R software (version 4.0.3) [21,22]. Categorical variables will be described with absolute frequencies and percentages, and continuous variables will be described with means and SDs or medians and quartiles. A 2-tailed *t* test will be used to compare the values related to pain, anxiety, and satisfaction across the two groups. The correlations between pain perception and anxiety values reported by the children and those reported by their caregivers and nurses will be evaluated by means of a Pearson correlation. The significance level will be set at 5%, and all CIs will be set at 95%.

The data will be stored in a database. The Pearson chi-square test will be used for the calculation of statistical significance.

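### Adding age/vaccine visit and arrival heart rate to the between-group comparison would gain precision at almost no cost; the planned unadjusted t test is valid but ignores them

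*Protocol article*

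**What the plan says.** **Test.** Under Statistical Analysis, the protocol article gives a two-tailed t test that "will be used to compare the values related to pain, anxiety, and satisfaction across the two groups". It names no covariate, baseline value or age stratum. Heart rate is not in that list, although the Results section makes a significant heart-rate difference part of a satisfactory result.

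**Population.** The Inclusion Criteria admit children due for one of two visits: "the triple viral+varicella vaccine at 3 years of age and (2) the hepatitis A+diphtheria-tetanus-pertussis vaccine at age 6". Each child attends one visit, so age and vaccine pair together form a single two-level covariate.

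**Randomization.** Sequence Generation and Implementation name the software and mention no stratification by visit.

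**Baseline data.** Under Data Collection, Sources of Information, and Intervention, age is recorded for each patient, and "the patients’ condition and heart rate on arrival at the clinic will be recorded, regardless of their assigned study group". The same section mentions data taken before and after the procedure. That sentence sits in the paragraph on the intervention group and does not name a scale.

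**Sample size.** No outcome is labelled primary; pain is the one used for sizing. "To detect a 1-point difference between the two groups on the pain level scale", the article says, "a sample of 150 boys and girls in each group is required", with an SD of 3, 5% alpha, 80% power and 5% loss.

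**The concern.** A 3-year-old and a 6-year-old may well differ in how they report pain and fear, and the two visits use different vaccines. If the visit predicts the outcome, an unadjusted comparison leaves the between-visit variance in the error term. Any chance difference between the arms in the share of 3-year-olds also stays in the estimated effect. For heart rate, the value on arrival is the natural baseline, and no use of it is stated.

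At stake is precision. A linear model with arm and baseline covariates still estimates the difference in mean scores between arms, usually with a smaller standard error. Here the data for the main covariates are already being collected.

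**Working it through.** **1. The plan's own figure.** Inputs from Sample Size Determination: difference 1 point, SD 3, two-sided 5%, power 80%, loss 5%.

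- n per group = 2 × (1.960 + 0.842)² × 3² / 1² ≈ 141.3, so 142.
- After 5% loss: 142 / 0.95 = 149.5, so 150. The stated 150 reproduces.
- Power at 142: standard error = 3 × √(2/142) = 0.356; 1/0.356 − 1.960 = 0.849; power = 80.2% (79.9% with the noncentral t).

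The unadjusted test therefore delivers its planned power.

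**2. Power with covariates.** The documents give no share of pain variance explained by baseline values (R²), so a range is assumed. Residual SD = 3 × √(1 − R²), put into the same formulas.

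| Assumed R² | Residual SD | Power at 142 per group | n per group for 80% power, after 5% loss |
|---|---|---|---|
| 0 | 3.00 | 80.2% | 150 |
| 0.05 | 2.92 | 82.2% | 143 |
| 0.10 | 2.85 | 84.1% | 135 |
| 0.20 | 2.68 | 88.1% | 120 |
| 0.30 | 2.51 | 91.9% | 105 |

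**3. Visit as the only covariate.** Assume equal numbers at 3 and 6 years and a gap of D points in mean pain. The visit then explains 0.25 × D² of the total variance of 9, so R² = 0.25 × D² / 9.

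| Assumed gap D | R² | Power at 142 per group |
|---|---|---|
| 1 point | 0.03 | 81.3% |
| 2 points | 0.11 | 84.6% |
| 3 points | 0.25 | 90.0% |

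**4. Chance imbalance.** With the same 50/50 mix and no stratification, the difference between arms in the share of 3-year-olds has standard error √(0.25 × 2/142) = 0.059. Its 95% range is ±1.96 × 0.059 = ±0.116, or 11.6 percentage points. Multiplied by a gap of 1, 2 or 3 points, this shifts the unadjusted difference by up to 0.12, 0.23 or 0.35 points, against a target of 1 point. For scale, the 95% half-width of the unadjusted difference is 1.96 × 0.356 = 0.70 points.

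**5. Simulation check.** With 20,000 trials per scenario, 142 per group and a 2-point gap, type I error was 5.2% for the t test and 5.0% for the visit-adjusted model. Power was 79.8% and 84.2%.

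**The case against.** **The t test is not wrong.** This stands. In a randomized trial it is a valid comparison, and this trial was sized for it. A reader might infer that the trial is underpowered or its estimate biased. The documents support neither: the sample size reproduces, and chance imbalance is random error already counted in the t test's standard error. The simulated error rates show the same.

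**The gain rests on assumptions.** This also stands. The R² values, the age gap and the 50/50 mix are not in the documents. If the visit is the only covariate and the gap is 1 point, the gain is about 1 percentage point of power.

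**Baseline scores are not established as covariates.** A reader might take the before-and-after sentence to mean that pain and fear are scored before vaccination in every child. It does not say so: it stands in the intervention-group paragraph and names no scale. It also follows the account of assignment, of telling the child about the device and of fitting it. In an open trial, a score taken at that point could already reflect the allocation, and adjusting for it could remove part of the effect under study.

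**An unseen analysis plan, or the full protocol, may add adjusted models or stratification.** That is possible. But the article does not leave the method open: it names the t test. If randomization was in fact stratified by visit, the case for including visit in the model would remain.

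**Conclusion.** The point holds as a free improvement, not as an error. The article fixes an unadjusted test for pain and anxiety although visit and arrival heart rate are available in both arms. Adjustment would lift power for pain from about 80% to between about 82% and 92% if the covariates explain an assumed 5% to 30% of the variance. For visit alone, with an assumed gap of 1 to 3 points and equal numbers at the two ages, the range is about 81% to 90%. It would also remove a chance age shift of up to 0.12 to 0.35 points (95% range, same assumptions) from the estimate. This is power beyond the planned 80%; no shortfall is being repaired. For heart rate the article names no test, so there the proposal specifies an analysis and does not replace one.

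**What to change.** Before the analysis begins, prespecify the following:

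- **Pain and fear:** a linear model of the post-injection score on arm and age/vaccine visit, with arrival heart rate as an optional further covariate.
- **Heart rate:** a linear model of the later value on arm, visit and arrival heart rate.
- **Sensitivity analysis:** the unadjusted two-tailed t test already named, for pain and fear.
- **Pre-vaccination fear or pain score:** include it only if it is taken in both arms before the child is told the allocation or fitted with the device. Otherwise leave it out.

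The cost is a change of wording and slightly more analysis work. Visit and arrival heart rate need no new data, and the sample size can stay at 150 per group.
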